# SCHEMA

Disease progression

Capecitabine (1000 mg/m^2^ bid po d1-14 q3w)

Apatinib (500 mg qd po)

(A treatment cycle lasts 21 days)

Sign the Informed Consent

Screening, check and inclusion

Patients with platinum-failure recurrent/metastatic NPC

Every 2 treatment cycles after taking the drugs, imaging examinations will be performed to assess the efficacy

Apatinib treatment will be terminated and survival follow-up will continue

Tumor reduction or stabilization

The original treatment regimen will be continued until the occurrence of disease progression or intolerable adverse reactions

# 1. STUDY BACKGROUND

Nasopharyngeal carcinoma (NPC) is one of the most common head and neck tumors in Southeast Asia, ranking first among malignant head and neck tumors in China, especially in southern China, including Guangdong, Guangxi, Fujian, Jiangxi and Hong Kong, where the NPC incidence is the highest in the world. For patients with early and locally advanced NPC, the standard treatment regimen is synchronous chemo-radiotherapy, with a five-year survival rate of 80% ^[1]^. However, there are still 8.6%-23.7% of patients who have a recurrence of nasopharyngeal and cervical lymph nodes within five years and need retreatment, and 65%-85% of patients relapse within three years after the first course of treatment ^[2]^. Besides, the lesion site of NPC is hidden and hard to notice, so 70% of patients are already at the advanced stage when discovered clinically, and the most majority of them have developed distant metastases, leading to poor prognosis.

## 1.1. There is No Standard Second-line Chemotherapy Regimen for Advanced Recurrent or Metastatic NPC

Due to the low incidence of NPC in Western countries, there is insufficient high-quality research to support the treatment of advanced NPC. So far, the platinum-containing chemotherapy based on cisplatin combined with 5-Fu has been used in early-stage patients, often serving as the first-line chemotherapy regimen. Other active drugs include paclitaxel, docetaxel, capecitabine, irinotecan, vinorelbine, gemcitabine and ifosfamide, which can be used in combination or monotherapy. The need for continuous venous perfusion and the poor convenience of the commonly used drug 5-Fu can easily cause venous infection, thrombosis and oral mucositis, which seriously affect the quality of life of patients.

In a phase II clinical study, Chen et al. ^[3]^ applied the triplet combination (TP) regimen as the first-line treatment for patients with recurrence and metastasis, achieving a response rate of 79%, with the mPFS and mOS being 8.6 months and 22.7 months, respectively. There was also a repor about the combination of lobaplatin with docetaxel as first-line chemotherapy for recurrent and metastatic NPC, which achieved an overall remission rate (ORR) of 61.5% and a mPFS of 10.0 months ^[4]^.

On August 23, 2016, *The Lancet* published online the results of a phase 3 clinical study by [name] and his team on gemcitabine plus cisplatin versus fluorouracil plus cisplatin for recurrent or metastatic NPC. The objective response rate of the GP group vs. the FP group was 64% vs 42%, the mPFS was 7.0 months vs. 5.6 months, the mOS was 29.1 months vs. 20.1 months, the risk of disease progression dropped by 45%, the risk of death decreased by 38%, and the total reverse reaction rate in the two groups was similar ^[5]^. [name] study provides new clinical data support for the first-line medication regimen for patients with recurrent or metastatic NPC.

The prognosis of recurring or metastatic NPC patients after the failure of first-line platinum-based therapy is poor. No well-established second-line or third-line regimens are available. Meanwhile, many patients are generally in bad conditions after the failure of platinum-based therapy and unable to tolerate combination chemotherapy due to the deterioration of ECOG score and nutritional status. In most cases, such patients become platinum-resistant, so it is difficult for them to continue to benefit from platinum-containing combination chemotherapy regimens. Clinically, single-drug therapy is often preferred, such as fluorouracil, paclitaxel and methotrexate.

Capecitabine is a new-generation oral fluoropyrimidine drug that can be rapidly absorbed gastrointestinally in the original form. It can be converted into 5-Fu with antitumor activity in the liver and cancer tissues to exert a cytotoxic effect. Thymidine phosphorylase (TP), the last enzyme in the activation process of capecitabine, can make 5-FU selectively activated in the tumor tissue and minimize the systemic exposure of 5-FU, thereby avoiding the damage of 5-FU to normal tissues. Peng et al. ^[6]^ treated recurrent or metastatic NPC patients with the combination chemotherapy of capecitabine and nedaplatin after the failure of the cisplatin-based first-line chemotherapy，the response rate reached 41.7%, mPFS and mOS were 5.8 months and 12.4 months, respectively. In another clinical study using capecitabine monotherapy to treat 49 advanced NPC patients (71% with distant metastasis), CR was 6%, PR was 31%, mPFS was 5 months, and mOS was 14 months ^[7]^. According to a study published in *British Journal of Cancer* in 2010, capecitabine monotherapy for patients with recurrent or metastatic head and neck squamous cell carcinoma^[8]^ was effective in 33 out of 40 cases, including 2 cases of CR, 6 cases of PR, 18 cases of SD, and mTTP was 4.8 months, mOS was 7.3 months, and ORR was 24.2%, which indicated that capecitabine could serve as an effective and safe drug to treat patients with recurrent or metastatic head and neck squamous cell carcinoma.

There are many options for palliative chemotherapy for recurrent or metastatic NPC, but most relevant studies have a small sample size, and there are neither sufficient large-scale prospective research data nor sufficient separate research data on recurrent NPC and distant metastasis. The research and development of high-efficiency, highly selective, low-toxicity and convenient therapies are urgently needed.

## 1.2. EGFR Inhibitors Have Proven Efficacies, but the High Price Limits Their Clinical Application

EGFR is a transmembrane glycoprotein that belongs to the HER family. The binding of its extracellular part to EGF can activate the tyrosine kinase in the cell membrane, thereby regulating cell growth and differentiation. The high expressions of EGFR and relevant ligand transforming growth factors are closely associated with the high invasiveness of tumors, high lymph node metastasis, short-term recurrence and survival. The expression of EGFR in different tumors varies. The positive rate of EGFR expression in NPC patients is significantly higher than that in the control group, and the EGFR positive rate increases as the differentiation of tumors becomes worse. The EGFR expression in NPC patients with cervical lymph node metastasis is notably higher than that in those without cervical lymph node metastasis ^[9, 10]^, indicating there is a certain relationship between EGFR and the occurrence of NPC, cancer cell differentiation and tumor progression.

Nimotuzumab is a monoclonal antibody drug targeting EGFR, and the effective rate of nimotuzumab in combination with radiotherapy in the treatment of advanced NPC can reach up to more than 90%. The Chinese version of the NCCN Guidelines for Head and Neck Cancers has recommended nimotuzumab as one of the regimens combining radiotherapy for NPC in 2010 ^[11]^. Cetuximab is an FDA-approved first-line therapeutic drug for recurrent/metastatic head and neck squamous cell carcinoma. Chan et al. ^[12]^ treated 60 recurrent/metastatic advanced NPC patients resistant to platinum treatment using cetuximab combined with carboplatin, and the results showed 20% of CR, 80% of PR, 100% of DCR, and 7.7 months of mOS 7.7. A retrospective study in 2016 ^[13]^ showed that among 30 recurrent or metastatic NPC patients treated with cetuximab in combination with concurrent chemo-radiotherapy (chemotherapy regimens including TP/TPF and GP/PC, etc.), 21 cases had clinical responses (70%), mOS was 23.6 months, PFS was 12.2 months, and the two-year OS reached 53.3%. Though cetuximab demonstrates good efficacy, the expensive treatment price, especially in developing countries, limits its clinical application.

## 1.3. PD-1 Antibody Immunotherapy Shows Preliminary Efficacy and Needs further Exploration

Chen et al. ^[14]^ reported that PD-L1 was expressed in 89% of EBV-associated NPC. A study on EVB-associated NPC ^[15]^ also found that PD-L1 was mainly expressed in EBV-positive NPC cells and a better local control rate could be achieved in patients with low PD-L1 expression. A retrospective study analyzed the relationship between the expression of PD-1/PD-L1 in NPC patients and the post-treatment outcome ^[16]^. Among the 139 advanced NPC patients receiving chemotherapy, it was found through tissue immunohistochemistry that 37.4% (52/139) of the cases had PD-1 expression and 95% (132/139) of the cases had PD-L1 expression, the DFS of patients with high PD-L1 expression was worse than that of patients with low PD-L1 expression (p = 0.009), and the DFS of patients with co-expression of PD-1 and PD-L1 was even worse (p = 0.038). The results suggested that PD-1/PD-L1 expressions could predict recurrence and metastasis of NPC after treatment, and blocking this pathway provided a potential therapy target for NPC.

On August 24, 2018, *JCO* published online a phase Ib clinical study on the use of Pembrolizumab in treating recurrent or metastatic NPC patients with PD-L1 expression ≥ 1% (keynote-028). 27 patients received pembrolizumab treatmentand were followed up for 20 months (median). The results showed that there were 7 cases of PR, 14 cases of SD, 25.9% of ORR, 8 cases (29.6%) of SAEs (Grade 3 and above) occurred including 1 case of drug-related death (sepsis) ^[17]^. Meanwhile, there are ongoing phase II clinical studies on the use of Nivolumab in advanced recurrent/metastatic NPC and the combined use of Nivolumab and Ipilimumab in EBV-positive advanced NPC.

## 1.4. Antiangiogenesis is An Important Target for Treating NPC

Angiogenesis, primarily regulated by vascular growth factors and vascular growth inhibitory factors, plays a vital role in the growth and metastasis of tumors. There are more than 20 vascular growth factors including EGF, VEGF and PDGF, among which VEGF is the most important one. VEGF binds to its receptor, activates the VEGFR-mediated downstream signal pathway, promotes mitosis and chemotaxis of endothelial cells, increases vascular permeability, and causes the extravasation of fibrinogen in blood vessels, which not only provides the essential matrix for endothelial cell migration and the establishment of neonatal capillary network, but also provides raw materials for tumor growth. Studies have shown that VEGF is over-expressed in 67% of NPC patients, and the high expression of VEGF is significantly correlated with the high recurrence rate of NPC and the survival of patients ^[18]^. The efficacy of antiangiogenic therapy in NPC has been verified to a certain extent.

A multicenter phase II clinical study ^[19]^ found that adding bevacizumab to standard chemo-radiotherapy for locally advanced NPC patients can delay the progression of subclinical NPC, and this regimen did not cause hemorrhage in Grade 3-4 patients. During the follow-up of 2.5 years (median), the two-year PFS rate was 74.7%, the two-year distant metastasis-free survival (DMFS) rate was 90.8%, and the two-year OS was 90.9%. Therefore, bevacizumab demonstrates certain advantages in both PFS and OS. According to a study where the recurrent or metastatic head and neck cancer/NPC patients were treated with sorafenib monotherapy ^[20]^, among 27 cases, there were 1 case of PR and 10 cases of SD, and mOS was 4.2 months. This indicated the limited efficacy of the sorafenib monotherapy and a combination with chemo-radiotherapy might be required. In another study of sorafenib combined with cisplatin and fluorouracil ^[21]^, 54 recurrent or metastatic NPC patients were treated with the combination therapy, mPFS was 7.2 months and mOS was 11.8 months, suggesting that the combination of sorafenib with chemotherapy is a feasible regimen for the treatment of metastatic NPC. A single-arm exploratory study of single-agent sunitinib [22] found that 10 out of 14 patients received imaging assessment at least once and tumor reduction was found in 5 cases, but 2 cases with tumor invasion of the carotid sheath died of hemorrhage during the experiment, and the possible cause might be the rupture of large cervical vessels during tumor regression.

Li Bin et al. ^[23]^ treated 30 metastatic NPC patients with endostar combined with chemotherapy (cisplatin + fluorouracil or gemcitabine + cisplatin) and found 4 cases of CR, 22 cases of PR, 3 cases of SD, 1 case of PD, clinical benefit rate of 96.7%, and objective response rate of 86.7%, suggesting that endostar combined with chemotherapy had good short-term efficacy and tolerability in the treatment of metastatic NPC. At CSCO 2015 International Antiangiogenic Therapy Forum, [name] and his team from Sun Yat-Sun University Cancer Center reported that among 22 patients who used Endostar combined with radiotherapy/chemotherapy in treating locally advanced recurrent NPC, 20 patients had CR and 2 patients had PR, with the tumor response rate up to 100% and the two-year OS of 66.4%, and that the combined therapy reduced the occurrence of nasopharyngeal mucosa necrosis, but did not shorten the OS, and to some extent improved the quality of life of recurrent NPC patients after treatment.

## 1.5. Apatinib may be a Potentially Effective Drug for Advanced NPC

Apatinib Mesylate is invested and developed by Jiangsu Hengrui Medicine Co., Ltd., with independent intellectual property rights. It is a small molecular tyrosine kinase inhibitor that mainly blocks the signaling pathway of VEGF binding to its receptors by highly selective inhibition of VEGFR-2 (vascular endothelial cell growth factor receptor 2) activity, thereby strongly inhibiting tumor angiogenesis and playing an anti-tumor effect. As a novel oral small molecular tyrosine kinase inhibitor, Apatinib can effectively inhibit VEGFR at very low concentrations, with the IC50 value of 2nM at the VEGFR2 target, 45 times that of Sorafenib and 5 times that of Sunitinib, while at high concentrations, it can also inhibit the platelet-derived growth factor receptor (PDGFR) and c-Kit and c-Src kinases.

The study of the subgroup analysis of Apatinib in a phase IV study on gastric cancer (Ahead-G201) published by Qin Shukui et al. ^[24]^ on ASCO-GI in 2018 showed that patients given 500 mg qd of the drug had fewer both total AEs and grade 3 to 4 AEs than those given 850 mg qd (P = 0.001), the mPFS of the two groups was 4.63 and 2.23 months, respectively (P = 0.0459), and the mOS was 6.83 and 4.04 months, respectively (P = 0.0083), proving that Apatinib at the dose of 500mg qd was sufficiently safe and effective in the real world.

Peng Qiuxia et al. ^[25]^ also found in NPC cell line CNE-2 transplantation tumor model that the combined use of Apatinib and cis-platinum could significantly inhibit tumor growth, extend survival, reduce VEGFR-2 expression, decrease microvessel density, with better efficacy than Apatinib alone. Moreover, VEGFR-2 was an important predictive marker for the efficacy of Apatinib in treating NPC. According to the study by Lin Yansong et al. ^[26]^, 10 patients with iodine-refractory differentiated thyroid carcinoma had their OOR and DCR up to 90% and 100% after receiving 750 mg qd of Apatinib monotherapy (*oncotarget*, 201702), and the main adverse reactions included hypertension, hand-foot-skin reactions and hypocalcemia. In 2017 *EMBO*, He Xiaohui et al. ^[27]^ reported a phase II prospective study on Apatinib monotherapy in the treatment of head and neck metastatic adenocarcinoma after multiple chemotherapies, and found that the ORR of 8 patients was 25%, the DCR was 87.5%, and the drug toxicity tolerable and controllable. Zhu Guopei et al. ^[28]^ from Shanghai Ninth People's Hospital reported the results of a phase II clinical study on Apatinib treating recurrent or metastatic adenoid cystic carcinoma at the 2018 Multidisciplinary Head and Neck Cancers Symposium (AHNS/ASTRO/ASCO), a total of 38 patients received 500 mg of Apatinib alone had an mPFS of 4.5 months, an ORR of 44.7%, and a DCR of 89.5%, suggesting the huge potential efficacy of Apatinib in treating head and neck tumors.

# 2. STUDY OBJECTIVES

The study objectiveis to evaluate the efficacy and safety of Apatinib plus Capecitabine combination therapy in treating patients with recurrent/metastatic NPCwho failed platinum-based therapies.

## 2.1. Primary Objective

The primary objective is to evaluate the objective response rate (ORR) of Apatinib plus Capecitabine combination therapy in treating patients with recurrent/metastatic NPC who failed platinum-based therapies.

## 2.2. Secondary Objective

Secondary objectives are disease control rate (DCR), duration of response (DOR), the progression-free survival (PFS), overall survival (OS), as well as the safety and tolerance of the therapy.

# 3. STUDY DESIGN

## 3.1. Study Design Description

This is a non-randomized, single-arm, open phase II clinical study to evaluate the efficacy and safety of Apatinib combined with Capecitabine therapy in treating patients with recurrent/metastatic nasopharyngeal carcinoma who failed platinum-based therapies.

If a patient does not withdraw the Informed Consent form, is not intolerant to the toxic side effects of the drug, or is not believed unsuitable for further trials by the investigator, he/she should continue the study and treatment until tumor progression with solid imaging evidence. Efficacy indicator and safety indicator will be observed in the study.

## 3.2. Study Drug

### 3.2.1. Medication Regimen

Oral medication of Apatinib of 500 mg, qd, with 4 weeks as a cycle; oral medication of Capecitabine of 1,000 mg/m^2^ once after breakfast and once after dinner every day for two consecutive weeks, with three weeks as a cycle.

With 3 weeks as a treatment cycle, patients will be given both drugs until PD, intolerant toxicity, death, withdrawal of the Informed Consent form, or discontinuity of drugs at the investigator's judgment.

### 3.2.2. Distribution and recycling of drugs

The study drug shall be uniformly stored, distributed and recycled by the study unit according to the GCP requirements. The drugs should be distributed and kept by special personnel, with strict management, and the receipt and use of them should be recorded in detail by the investigator during each visit.

When distributing drug to a patient on the first day of each cycle, from the first day of the first cycle when the patient receives free medication, the investigators should:

- State the number of Apatinib tablets to be distributed to the patient in the next treatment cycle;

- Fill such information (the number of Apatinib tablets to be distributed) in the CRF page of the study drug, and record in the drug distribution logbook.

Instruct patient to obey the treatment regimen, and return all unused tablets and all drug packages (including empty boxes and remaining tablets) at each visit to the hospital.

The total quantity of the trial drugs will be 120% of the designed dose. The investigator must ensure that all study drugs are used only in subjects participating in the clinical trial, and unused drugs will be returned to the sponsor, Jiangsu Hengrui Medicine Co., Ltd. after the end of the trial, with remaining drugs and empty drug packages to be collected by the monitors. The study drugs cannot be given to anyone not participating in the clinical trial.

## 3.3. Sample Size Estimation

This study is a superiority trial using Simon's two-stage design to estimate the sample size. One-sided alpha is 0.05, beta is 0.2, and the testing power is 0.8. According to literature, the ORR of capecitabine monotherapy is 24.2%, assuming that the ORR of the combination of apatinib and capecitabine increases by 15%, i.e., ORR = 39.2%, given a 10% drop-out rate, at least 64 cases are needed. In the first stage, 31 cases will be enrolled, when the number of effective cases is ≤ 7, it is considered that the efficacy of the drug combination is not better than the monotherapy, and the trial will be terminated. Otherwise, continue to the second stage of enrollment.

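### The 24.2% null comes from head and neck squamous cancer and its choice is not justified, so beating it would not show benefit over capecitabine alone in NPC

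*Protocol*

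**What the plan says.** Section 3.3 describes the design in these terms: "This study is a superiority trial using Simon's two-stage design to estimate the sample size". The null rate is introduced with "According to literature, the ORR of capecitabine monotherapy is 24.2" per cent, with no tumour type named. The alternative follows: "assuming that the ORR of the combination of apatinib and capecitabine increases by 15%, i.e., ORR = 39.2" per cent. The error rates are "One-sided alpha is 0.05, beta is 0.2, and the testing power is 0.8", and the size is "given a 10% drop-out rate, at least 64 cases are needed". Stage 1 enrols 31 patients. With 7 or fewer responders the trial stops and "it is considered that the efficacy of the drug combination is not better than the monotherapy". The synopsis frames the decision in the same way.

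The source of the null is in section 1.1. There, 24.2% is the ORR reported for "capecitabine monotherapy for patients with recurrent or metastatic head and neck squamous cell carcinoma". The title of that study in the References shows that its patients had already received platinum. The sentence before it in section 1.1 describes "capecitabine monotherapy to treat 49 advanced NPC patients (71% with distant metastasis), CR was 6%, PR was 31" per cent; it does not say how many of those 49 patients had failed platinum. The trial itself enrols only NPC that has failed platinum-based therapy (section 3.4.1, criteria 1 and 2).

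**The concern.** A single-arm trial has no control group, so the null rate does all the comparative work. Section 3.3 presents 24.2% simply as the rate for capecitabine monotherapy and reads the result as better or not better than that drug alone. A reader of section 3.3 would not learn that the rate belongs to a different tumour, or that the same protocol reports a higher rate for the same drug in NPC.

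If capecitabine alone achieves more than 24.2% in this population, the trial can meet its criterion with apatinib contributing nothing. The primary conclusion would then be read as a benefit of the combination that the design cannot show.

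**Working it through.** **Inputs.** From section 3.3: p0 = 0.242, p1 = 0.392, one-sided alpha 0.05, power 0.80, n1 = 31 with a stop at 7 or fewer responders, N = 64 including 10% drop-out. From section 1.1: in the squamous-cancer study, 2 CR + 6 PR = 8 responders and ORR 24.2%; in the NPC study, CR 6% and PR 31% of 49.

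**1. Reproduce the design.** An exact binomial search over Simon two-stage designs with these inputs gives the minimax design n1 = 31, r1 = 7, n = 58, r = 19. Its exact alpha is 0.0495 and its power 0.8002. Then 58 × 1.1 = 63.8, rounded up to 64 (58 / 0.9 would give 65). The optimal design (7/26, 22/70) does not match. The protocol's figures are therefore reproduced by the minimax design.

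**2. Final cut-off.** The protocol states none. The matching design declares success at r + 1 = 20 responders, and 20/58 = 34.5%. This cut-off is a reconstruction.

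**3. The two benchmarks** (exact Clopper-Pearson 95% CIs).

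| Source | Rate | 95% CI |
| --- | --- | --- |
| Squamous cancer, platinum-pretreated | 8/33 = 24.2% | 11% to 42% |
| NPC, prior platinum not stated | 6% + 31% = 37%; about 18/49 = 36.7% | 23% to 52% |

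Each interval contains the other estimate. The reconstructed threshold of 34.5% lies below 37%, and the target of 39.2% lies 39.2 − 37 = 2.2 points above it.

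**4. Chance of success if apatinib adds nothing.** For a true rate p,

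P(success) = Σ over x from 8 to 31 of P(X1 = x) × P(X2 ≥ 20 − x),

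with X1 ~ Bin(31, p) and X2 ~ Bin(27, p). The chance of stopping at stage 1 is P(X1 ≤ 7).

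| True capecitabine ORR in this population | P(success), 20/58 | P(stop at stage 1) |
| --- | --- | --- |
| 24.2% | 0.05 | 0.51 |
| 30% | 0.26 | 0.24 |
| 35% | 0.57 | 0.10 |
| 37% | 0.69 | 0.07 |

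**5. Sensitivity to the reconstruction.**

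- At 18/49 instead of 37%, P(success) is 0.68.
- If all 64 patients are evaluable, the smallest cut-off holding alpha at or below 0.05 is 22/64 (alpha 0.042). P(success) at 37% is then 0.70.
- Section 3.11.4 specifies two-sided tests and Clopper-Pearson 95% intervals. If success means a lower limit above 24.2%, the cut-off is 22/58 (lower limit 25.5%; 21/58 gives 24.0%) or 23/64 (24.3%; 22/64 gives 23.0%). With the stage 1 rule kept, P(success) at 37% is 0.49 or 0.61.

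**The case against.** The strongest defence is that 24.2% was matched on treatment line. The cited squamous-cancer patients had received platinum, and platinum failure defines this trial's population. Section 1.1 itself says that NPC patients who have failed platinum do poorly and are often in worse condition, so a rate below 37% is plausible for them. This stands as a possible reason, but the protocol never gives it.

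A reader might go further and infer that 24.2% is the wrong null and 37% the right one. The documents do not support that. The 37% rests on 49 patients of unstated platinum history, its interval includes 24.2%, and the two series do not differ detectably (18/49 against 8/33, Fisher p = 0.33). The 0.69 is conditional on one value, which is why a range is shown.

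Nor does the denominator help that reading. The 24.2% is 8/33, and on the 40 patients also mentioned it would be 8/40 = 20%. That would lower the null, not raise it.

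It is also fair that the synopsis calls the study exploratory, that the primary objective is to evaluate ORR, and that section 3.11.4 describes mainly descriptive analysis. The ORR and its interval remain valid whatever the benchmark. The fault lies in the superiority wording and the unexplained null.

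**Conclusion.** The concern holds as an unjustified benchmark combined with a claim stronger than the design supports. The test is whether ORR exceeds a rate from squamous cancer. Meeting it would not show benefit over capecitabine alone in NPC.

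Under the reconstructed 20/58 rule, the chance of success with no apatinib effect runs from 0.26 to 0.69 as the true capecitabine rate runs from 30% to 37%, against a nominal 0.05. With the confidence-limit reading it is 0.49 to 0.61 at 37%. These figures assume that the minimax match is the design intended and that the stage 1 rule is applied as written. They do not assume that 37% is the true rate, which the documents do not establish.

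Severity: should fix. The response estimate is unaffected; what it may be said to show is affected.

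**What to change.** 1. In section 3.3 and the synopsis, replace the superiority label and the comparison with monotherapy by wording such as: *the study tests whether ORR exceeds 24.2%, the rate reported for capecitabine in platinum-pretreated recurrent/metastatic head and neck squamous cancer*.
2. Add a sentence saying why that rate was preferred to the NPC figure in section 1.1.
3. Report the ORR with its 95% CI against both 24.2% and 37%, and make no claim of superiority over capecitabine alone in NPC.

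The cost is a more modest claim and a few lines of text. No extra patients and no re-sizing are needed.

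A fixed bar that puts the lower 95% limit above 37% is not recommended. It would need 32/64 (lower limit 37.2%; 31/64 gives 35.8%), and at the protocol's own target of 39.2% the chance of reaching it is about 5%. It would also turn an uncertain 49-patient estimate into a decision rule, and no single-arm threshold can establish superiority over a drug not given alone in the trial.

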# PROTOCOL SYNOPSIS

| **Study Drug** | Apatinib plus Capecitabine |
| --- | --- |
| **Study Title** | A Phase II Study to Evaluate the Efficacy and Safety of Apatinib in Combination with Capecitabine in Patients with Recurrent/Metastatic Nasopharyngeal Carcinoma Who Failed Platinum-based Therapies |
| **Investigator** | [name]; [name] |
| **Protocol Version** | 2.2 |
| **Protocol Date** | October 29, 2018 |
| **Study Design** | A non-randomized, open-label, single-arm exploratory study |
| **Study Properties** | A clinical study initiated by the investigator |
| **Study Subjects** | Patients with recurrent/metastatic advanced nasopharyngeal carcinoma (NPC) who failed platinum-based therapies |
| **Study Objective** | To evaluate the efficacy and safety of apatinib combined with capecitabine in the treatment of patients with recurrent/metastatic advanced NPC who failed platinum-based therapies |
| **Study Sample Size** | This study is a superiority trial using Simon's two-stage design to estimate the sample size. Alpha is 0.05, Beta is 0.2, and the testing power is 0.8. According to literature, the ORR of capecitabine monotherapy is 24.2%, assuming that the ORR of the combination of apatinib and capecitabine increases by 15%, i.e., ORR = 39.2%, and the drop-out rate of 10%, at least 64 cases are needed. In the first stage, 31 cases will be enrolled, when the number of effective cases is less than 8, it is considered that the efficacy of the drug combination is not better than the monotherapy, and the trial will be terminated. Otherwise, continue to the second stage of enrollment. |

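### The 10% drop-out allowance is built into the total of 64 but not into the 31-patient first stage, so 31/64 enrolled has about 76% power, not 80%, if drop-outs yield no response

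*Protocol*

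**What the plan says.** Section 3.3 names the method: "This study is a superiority trial using Simon's two-stage design to estimate the sample size". Its error rates are "One-sided alpha is 0.05, beta is 0.2, and the testing power is 0.8". The null ORR is 24.2%, taken from capecitabine monotherapy, and the target is 15 points higher, 39.2%.

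On size it says "given a 10% drop-out rate, at least 64 cases are needed", and on the interim look "In the first stage, 31 cases will be enrolled, when the number of effective cases is ≤ 7", in which case the trial ends. The synopsis has the same total, "the drop-out rate of 10%, at least 64 cases are needed", and the same stage 1 rule in other words: "In the first stage, 31 cases will be enrolled, when the number of effective cases is less than 8".

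Neither place gives the total before inflation, the inflation formula or the final success boundary, or says whether the 31 are enrolled patients regardless of evaluability. The synopsis defines the ITT population as everyone enrolled. Section 3.11.3 defines the full analysis set as everyone dosed at least once, with the last observation carried forward for incomplete cases.

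**The concern.** A drop-out allowance on the total implies that the design counts evaluable patients and that enrolment must exceed that count. The same reasoning applies to stage 1, because a threshold of 7 responses is calibrated to a particular number of evaluable patients. Here the total is expressed as patients enrolled, while the stage 1 figure matches the evaluable count of the underlying design but is also described as enrolled.

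Two things are at stake. The underlying design has almost no slack (80.02%), so a small shortfall takes power below the stated value. And a stop at 7 or fewer out of roughly 28 evaluable patients is a harsher rule than the same stop out of 31, so an effective regimen is more likely to be abandoned at the look.

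**Working it through.** **Inputs (section 3.3).** p0 = 0.242, p1 = 0.392, one-sided alpha 0.05, power 0.80, drop-out 10%, n1 = 31, stop if responses ≤ 7, total 64.

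**Formula.** For stage 1 size n1, stage 1 boundary r1, total n and final boundary r (success if responses > r):

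P(success | p) = Σ over x from r1+1 to n1 of Bin(x; n1, p) × P[Bin(n − n1, p) > r − x]

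P(stop at stage 1 | p) = P[Bin(n1, p) ≤ r1]

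**Step 1: recover the plan's design.** An exact search for alpha ≤ 0.05 and power ≥ 0.80 finds no two-stage design with fewer than 58 patients. At n = 58, the design with the smallest expected size under p0 (44.1) is n1 = 31, r1 = 7, r = 19, with alpha 0.0495 and power 0.8002. This matches the stated 31 and ≤ 7. The values 58 and 19 are reconstructed, not quoted.

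**Step 2: the total.** 58 x 1.1 = 63.8, which rounds up to 64. 58/0.9 = 64.4, which is 64 to the nearest whole number and 65 rounded up. Either route gives the printed 64. At 10% drop-out, 64 x 0.9 = 57.6, just under 58; the chance that 64 enrolled give at least 58 evaluable is 0.54.

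**Step 3: stage 1.** 31 is the uninflated figure. 31 x 0.9 = 27.9 evaluable. With an allowance, 31/0.9 = 34.4, so 35 enrolled.

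**Step 4: operating characteristics at ORR 39.2%.** If each enrolled patient has a 10% chance of yielding no response, the response probability per enrolled patient is 0.9 x 0.392 = 0.3528. With the boundaries fixed as response counts, it makes no difference whether such patients are removed or counted as non-responders.

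| Stage 1 / total | Boundaries | Power | Stop at stage 1 |
|---|---|---|---|
| 31 / 58 evaluable | 7 / 19 | 80.0% | 4.0% |
| 28 / 58 evaluable | 7 / 19 | 78.0% | 8.7% |
| 28 / 57 evaluable | 7 / 19 | 75.6% | 8.7% |
| 31 / 64 enrolled, 10% without response | 7 / 19 | 76.0% | 9.5% |
| 31 evaluable / 64 enrolled, 10% random drop-out | 7 / 19 | 78.1% | 4.0% |
| 31 / 64 enrolled, drop-out costs no responses | 7 / 21 | 81.1% | 4.0% |
| 31 / 64 enrolled, 10% without response | 7 / 21 | 59.6% | 9.5% |

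The boundary of 21 is the one that keeps alpha within 0.05 when all 64 patients are analysed and none loses a response (alpha 0.042).

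**Step 5: what restores 80%.** With boundaries 7/19 and 10% drop-out, correcting only the total (31/65 enrolled) gives 78.0%. Correcting only stage 1 (35/64) gives 78.3%. Correcting both (35/65) gives 80.6%, but alpha averages 0.057, because a boundary of 19 is too low once more than 58 patients are evaluable.

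**The case against.** The strongest reply is that 76% is one scenario, not a property of the document. It needs the 31 to be read literally as enrolled, the reconstructed boundary of 19, and drop-outs who contribute no response. The protocol points partly the other way on the last. Patients withdrawn for excessive suspension still have their tumour evaluated (section 3.6). Those stopping without imaging progression are scanned every two cycles (section 3.8.3). The full analysis set carries the last observation forward (section 3.11.3), so a patient who leaves after responding can still count. If drop-out costs no responses, 31/7 with 64/21 has 81.1% power. If the look is made on 31 evaluable patients, the false-stop risk stays at 4.0%. All of this stands, and it is why the 76% is conditional.

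It does not remove the point. An allowance for drop-out has a purpose only if drop-out loses information, and the plan makes that allowance for the total alone. Keeping drop-outs in the denominator under ITT does not help if they have no response: power is 76.0% with a boundary of 19 and 59.6% with 21.

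A reader might also infer from 64, rather than 65, that the total was inflated with the wrong formula. The documents do not support that. No formula is given, and 64 fits 58/0.9 rounded to nearest as well as 58 x 1.1 rounded up. The text also says at least 64, which does not bar 65. Nor is the unstated final boundary a fault in itself, since an analysis plan may hold it.

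**Conclusion.** The point holds in limited form. Stage 1 carries no drop-out allowance, although the total does and both are described as patients enrolled. If drop-outs yield no response, the reconstructed boundaries 7/19 apply and the 31 are literally enrolled, power is about 76% at the plan's own drop-out rate (75.6% to 78.0% with 28 evaluable at stage 1 and 57 or 58 in total). The risk of stopping at stage 1 under the target ORR then roughly doubles, from 4.0% to about 9%.

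The stated 80% is kept only if drop-out costs no responses, or if the look uses 31 evaluable patients and at least 58 are evaluable in total. The protocol commits to neither. The marginal total is a secondary matter of one patient, although near 58 that patient is worth between two and three points of power (80.0% with 31 then 58 evaluable, 77.3% with 31 then 57). An arithmetic error in the inflation is not established.

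**What to change.** In section 3.3 and the synopsis, do one of the following.

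1. State that the 7-or-fewer rule applies to the first 31 response-evaluable patients (about 35 enrolled) and set the planned total at 65 (58/0.9, rounded up). Make the final decision on exactly 58 evaluable patients, with success at 20 or more responses. If a different number is analysed, re-derive the boundary, because 19 held fixed with more than 58 evaluable takes alpha above 0.05. Applied to exactly 31 and 58 evaluable patients, the rule has alpha 0.0495 and power 0.800.
2. Keep 31 and 64 enrolled, and restate power as about 76% under 10% drop-out with no response from those patients.

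The first option costs wording, one more planned patient and a stage 1 look about four enrolments later. The second costs only a less favourable stated power, and leaves the false-stop risk at about 9%.
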